#### 2.2.1. The Intervention: Neurolinguistic Programming and Sophrology

Each participant will benefit from an NLP and sophrology intervention. The sophrology/NPL program will be provided by a qualified sophrologist outside from the hospital and that will be specifically employed by Clermont-Ferrand University Hospital for the purpose of this study, in order to avoid any previous relation between volunteers and the therapist. NLP and sophrology will take place within the University Hospital of Clermont-Ferrand. A total of 6 to 8 sessions will be proposed for each participant, by group of up to fifteen participants. Two sophrology sessions will be offered per week at two different times for easier accessibility. Each session will last one hour. They can take place in a seated or standing position, without physical contact. The sessions will consist of breathing exercises, visualization, and dynamic relaxation as well as concentration exercises. Breathing exercises have two objectives: (1) to manage the stress using deep inspiration and short expiration; (2) to dynamize the body using pauses between inspiration and expiration. During visualization process, we will ask participants to think of something or someone reminding pleasure and sensation of fullness. Dynamic relaxation includes exercises mobilizing parts of the body in order to take consciousness of all body segments. Breathing exercises, visualization, and dynamic relaxation are tools that should lead to an improvement of the dimensions of concentration (physical, mental, and emotional). All exercises will be guided by sophrologist. The sophrology/NLP program is standardized. Each session will take place in a typical way: (i) dialogue between the sophrologist and the participants, which makes it possible to specify the objective(s) of the session as the sophrologist will ask more specific questions to adapt the content of the sophrology session that they propose if they think it will be useful; (ii) presentation of the conduct of the session (possible variations) and instructions promoting autonomy; (iii) this practice is guided by the sophrologist, with the goal being to help free individuals from tensions, to play down a situation that worries and finally to realize that we can deal with. Sophrology exercises are adapted to the difficulties encountered by the participants; and (iv) time for free expression after the practice to promote the integration of the technique while giving elements to the sophrologist to guide the rest of the sessions.

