## 3. Results

### 3.1. Justification of the Sample Size

This study aims to demonstrate an improved heart rate variability in the intervention group, in comparison with the control group. According to previous data [32], it seems reasonable to estimate that effect size, for the primary analysis between M1 and M3, will be around 0.5 for HRV parameters. Effect sizes are considered small between 0.20 and 0.50, moderate between 0.50 and 0.80, and high above 0.80 [33]. To highlight such clinically relevant difference, 85 participants per randomized group will be needed for a two-sided type I error at 5% (alpha level, i.e., showing a difference that does not exist), a statistical power at 90%. If the desired power level is typically 80%, we specified a higher power level of 90%, so there would be a 90% probability that we will not commit a type II error (beta-level, i.e., failing to show a real difference) [34,35]. Finally, it is proposed to include 100 patients per group to consider loss to follow-up.

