#### 3.3.1. Analyses for the Primary Outcome

To compare the primary endpoint between groups, we will use Student’s t-test, or the non-parametric Mann–Whitney test if assumptions of t-test are not met. 

For the primary analysis, the intention-to-treat analysis will be considered, i.e., the comparisons between groups (“intervention” group and “waiting list” group) between M1 and M3. To prevent attrition bias, imputation of the missing data is planned. Then, the analysis of the primary outcome will be completed by multivariable analysis using a linear mixed model to compare HRV parameters between randomized groups considering (i) covariates identified according to clinical relevance (such as sex, age, number of complete sessions performed, occupational characteristics) and univariate results and (ii) session as random effects (to measure the variability between and within session). We will study the normality of the residuals from linear regression. If needed, a logarithmic transformation of the dependent variable will be suggested. Effect sizes and 95% confidence intervals will be used to express result. 

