#### 3.3.2. Analyses for the Secondary Outcomes

Randomized groups comparison will be carried out (i) as aforementioned for continuous secondary endpoints and (ii) for categorical endpoints using Fisher exact tests or chi-squared. The results will be introduced using median difference and 95% confidence intervals estimated using quantile regression model for non-Gaussian data. The results will be presented using absolute differences and 95% confidence intervals for categorical parameters. The multivariable analysis related to dichotomous endpoints will be generalized linear mixed model, with logit link function, and center as random-effect. The results will be expressed with of relative risks and 95% confidence intervals.

Longitudinal data will be analyzed using random-effects regressions, modeling between and within participant effect, as random-effect, in addition to session effect. These analyses will concern (i) within groups comparisons between and M0 to M7 by randomization group and (ii) between groups: comparisons at M5 and then between M0 and M7). For between groups comparisons, the following fixed effects will be studied: randomization group, time-points evaluation and their interaction. 

Subgroup analyses will be conducted to explore potential influence of sex, occupation, stress at baseline, and previous sophrology experience on the primary outcome. Interaction terms in the regression models will be used to test for heterogeneity of effect between subgroups.

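### The mixed model that completes the primary analysis names session as its only random effect and omits the participant, and neither the t-test nor the sample size allows for sophrology being delivered in groups.

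*Protocol article*

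**What the plan says.** All references are to the Protocol article.

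- **Endpoint and main test.** Section 2.6 sets the main outcome as the change in HRV from M1 to M3. Section 3.3.1 compares it between arms by Student's t-test, or Mann–Whitney if the assumptions fail.
- **Follow-on model.** Section 3.3.1 then completes this with a multivariable linear mixed model of HRV parameters, with "session as random effects (to measure the variability between and within session". No other random effect is named.
- **Contrast.** Section 3.3.2 describes the longitudinal random-effects regressions as "modeling between and within participant effect, as random-effect, in addition to session effect".
- **Measurements.** Section 2.6 and Table 1 schedule HRV at each of the 6 to 8 sessions and monthly otherwise. Under section 2.2 the waiting-list arm has no intervention for its first 3 months, so it has no sophrology sessions between M1 and M3.
- **Delivery.** Section 2.2.1: "A total of 6 to 8 sessions will be proposed for each participant, by group of up to fifteen participants". Two time slots are offered each week. Fixed membership of a group is not stated.
- **Sample size.** Section 3.1 assumes that the effect size "will be around 0.5 for HRV parameters" and concludes that "85 participants per randomized group will be needed" at two-sided 5% and 90% power, raised to 100 for loss to follow-up. Clustering is not mentioned.

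**The concern.** Two sources of correlation are not handled.

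**Within a person.** A model that separates variability between and within sessions presupposes several HRV values per participant, and values from one person are correlated. With session as the only random effect, that correlation is left out, and the named term has no evident meaning for half of the primary comparison. The adjusted estimate would carry a standard error that does not match the data.

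**Within a sophrology group.** Section 2.2.1 describes dialogue between the sophrologist and participants, exercises adapted to the difficulties raised, and a period of free expression. Participants who share sessions may therefore respond alike. Between M1 and M3 this applies to the intervention arm alone (a partially nested design). It affects the t-test on change scores as well as the mixed model, because both treat intervention participants as independent.

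At stake are the true error rate of the primary comparison and the power claimed for it.

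**Working it through.** **1. The plan's own figure.** Inputs from section 3.1: standardised difference 0.5, two-sided 5%, power 90%.

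n per arm = 2(1.960 + 1.282)² / 0.5² = 84.06, rounded up to 85. At 85 per arm, power = Φ(0.5/√(2/85) − 1.96) = Φ(3.260 − 1.96) = 90.3% (90.0% by noncentral t). The figure reproduces for independent participants. Going from 85 to 100 corresponds to 15% loss (85/0.85 = 100).

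**2. Participant effect omitted, group main effect on repeated levels.** The within-person correlation r is assumed (the documents give none). k1 and k0 are the values per participant in the intervention and control arms.

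True/naive variance = [(r + (1−r)/k1) + (r + (1−r)/k0)] / (1/k1 + 1/k0); real type I error = 2[1 − Φ(1.96/√ratio)].

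| k1 / k0 | r | Variance ratio | Type I error |
|---|---|---|---|
| 2 / 2 | 0.3 | 1.30/1.00 = 1.30 | 8.6% |
| 2 / 2 | 0.5 | 1.50/1.00 = 1.50 | 11.0% |
| 2 / 2 | 0.7 | 1.70/1.00 = 1.70 | 13.3% |
| 7 / 2 | 0.5 | 1.321/0.643 = 2.06 | 17.2% |
| 7 / 3 | 0.5 | 1.238/0.476 = 2.60 | 22.4% |
| 8 / 3 | 0.7 | 1.538/0.458 = 3.35 | 28.5% |

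**3. Participant effect omitted, group-by-time effect on M1 and M3 levels.** With total variance σ² and n per arm, the difference in change has true variance 4σ²(1−r)/n against a naive 4σ²/n, so the ratio is 1 − r. At r = 0.5 the real type I error is 2[1 − Φ(1.96/√0.5)] = 0.6%, and at r = 0.7 it is lower still. Here the standard error is too large.

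**4. One change score per participant.** There is no repetition within a person, so no participant effect is needed.

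**5. Group delivery ignored.** Groups of m = 15 in the intervention arm only, ICC assumed, total variance held fixed. DEFF = 1 + 14 × ICC. Power with a correct standard error = Φ(0.5/√((1+DEFF)/n) − 1.96). Type I error of the unadjusted test = 2[1 − Φ(1.96√(2/(1+DEFF)))].

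| ICC | DEFF | Type I error | Power, 85 per arm | Power, 100 per arm |
|---|---|---|---|---|
| 0.01 | 1.14 | 5.8% | Φ(3.151 − 1.96) = 88.3% | 92.8% |
| 0.05 | 1.70 | 9.2% | Φ(2.805 − 1.96) = 80.1% | 86.1% |
| 0.10 | 2.40 | 13.3% | Φ(2.500 − 1.96) = 70.5% | 77.4% |

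With Satterthwaite degrees of freedom, which reflect the small number of groups, power is 84.0%, 72.8% and 60.9% at 85 per arm, and 90.0%, 80.8% and 69.7% at 100. With groups of 8 and 85 per arm, the normal approximation gives 89.3% at ICC 0.01 and 80.1% at ICC 0.10.

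**The case against.** A reader might infer that the missing participant effect makes the primary test anti-conservative and so destroys the 90% power. The documents do not support that.

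- The main test is a t-test or Mann–Whitney on one change per person, which needs no participant effect. The mixed model only completes it.
- The 90% power belongs to that two-group comparison and reproduces. A standard error that is too small raises the rejection rate; it does not by itself lower power.
- The larger type I figures in step 2 need repeated levels to be pooled and a group main effect to be tested. The article fixes neither, and steps 3 and 4 show the problem reversing or vanishing under other layouts.

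All of this stands. What remains is that the model as worded fits repeated HRV values under neither estimand, and that it differs from section 3.3.2.

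On clustering, the objections are also fair in part. No ICC is given, fifteen is a maximum, and the two weekly slots mean that membership may not be fixed. A session effect coded as the actual group session could absorb some of the correlation, but the article does not define it, and the t-test has no such term. At ICC 0.01 with all 100 per arm analysed, power is still at least 90%. The clustering point is therefore conditional.

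A separate statistical analysis plan, not shown, may give the full specification. The article nonetheless states a random-effects structure for this model, and that statement should be correct.

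**Conclusion.** The point holds in a limited form, in two parts.

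**Participant effect.** The follow-on mixed model in section 3.3.1 is misspecified if it uses repeated HRV values. The direction of the error depends on what is tested: about 9–13% type I error (two values per arm, r 0.3–0.7) or about 17–28% (7–8 against 2–3 values, r 0.5–0.7) for a group main effect, and below 1% (r 0.5–0.7) for a group-by-time effect on M1 and M3 levels. The t-test on change scores is not affected by this omission.

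**Group delivery.** This does reach the t-test and the sample size. Assuming stable groups of 15 and ICCs of 0.01, 0.05 and 0.10, the nominal 5% test runs at about 6%, 9% and 13%. Power is about 88%, 80% and 71% with 85 per arm, or 93%, 86% and 77% with 100. Smaller groups shrink the effect. The documents do not establish that 90% power is missed, only that it rests on an unstated assumption of no clustering.

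**What to change.** 1. In section 3.3.1, add a participant random intercept wherever repeated HRV values are used, in line with section 3.3.2. Keep session only if it is defined for both arms.
2. Record which sophrology group or intake wave each participant attends. This must be done during the trial, because it may not be recoverable later.
3. In the between-group comparison of the M1–M3 change, allow for that grouping in the intervention arm by a random effect with small-sample degrees of freedom, at least alongside the t-test.
4. In section 3.1, state that 90% power holds without clustering, and give power over a range of ICCs.

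The cost is changed wording and one extra recorded variable, with no extra enrolment. The downside is slightly wider intervals and a less favourable stated power.

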#### 3.3.2. Analyses for the Secondary Outcomes

Randomized groups comparison will be carried out (i) as aforementioned for continuous secondary endpoints and (ii) for categorical endpoints using Fisher exact tests or chi-squared. The results will be introduced using median difference and 95% confidence intervals estimated using quantile regression model for non-Gaussian data. The results will be presented using absolute differences and 95% confidence intervals for categorical parameters. The multivariable analysis related to dichotomous endpoints will be generalized linear mixed model, with logit link function, and center as random-effect. The results will be expressed with of relative risks and 95% confidence intervals.

Longitudinal data will be analyzed using random-effects regressions, modeling between and within participant effect, as random-effect, in addition to session effect. These analyses will concern (i) within groups comparisons between and M0 to M7 by randomization group and (ii) between groups: comparisons at M5 and then between M0 and M7). For between groups comparisons, the following fixed effects will be studied: randomization group, time-points evaluation and their interaction. 

Subgroup analyses will be conducted to explore potential influence of sex, occupation, stress at baseline, and previous sophrology experience on the primary outcome. Interaction terms in the regression models will be used to test for heterogeneity of effect between subgroups.

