### 2.2. Study Settings

We will recruit any HCW or any NHCW from a healthcare institution (such as CHU of Clermont-Ferrand, other hospitals, clinics, retirement homes, EHPAD, etc.), who will be randomized in two groups: (i) the intervention group will have a longitudinal follow-up of seven months in total (a control period of 1 month, then 6 to 8 sophrology sessions during two months, then a 4-month follow-up); (ii) the control group will have a differed intervention (longitudinal follow-up of seven months in total beginning by a control period without intervention of 3 months, then 6 to 8 sophrology sessions during two months, then a 2-month follow-up).

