
#### 2.2.2. Description of Logistics Organization of the Study

Participants will benefit from NLP and sophrology interventions at the hospital. All measures will be conducted at the CHU Clermont-Ferrand. During the study, if a participant expresses particular psychic difficulties, support will be offered to him: appointment with the psychologist of the occupational health service of the CHU or referral to the attending physician according to his wishes.

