### 2.5. Recruitment Process

The study will be first proposed to workers of the University Hospital of Clermont-Ferrand (CHU)) using the mailing list of the staff. If there are not enough volunteers, then the study will be expanded to include all healthcare professionals. Volunteers will send an email with their contact to the address [contact]. A Clinical Research Assistant will contact them back and give them a first quick explanation of the study by phone, and will send them the information letter, so they can read it prior to the inclusion visit. Investigators will undergo the inclusion visits, either physically or by teleconsultation. Investigators will explain to each volunteer, in an exhaustive, clear and adapted manner, the research procedure, the potential benefit and the adverse effects taking into account their specificity (state of health, age, profession, habits and life projects, family environment, etc.) and will answer all questions. Participants can sign the consent form either during the consultation or later after a reflection period of 8 days. In this case, or for teleconsultation, the two signed consent forms will be returned by post or internal mail to the investigator. The investigator will keep one form, and the second form with both signature (investigator and volunteer) will be given to the volunteer at the baseline measure. They will be informed of the possibility, once their consent has been given, to withdraw it at any time.

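### Dichotomous secondary endpoints: a logit-link model is to be reported as relative risks with no conversion named, and its only random effect is an undefined centre

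*Protocol article*

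**What the plan says.** Section 3.3.2 of the protocol article deals with categorical secondary endpoints in three steps.

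- Unadjusted comparison: chi-squared or Fisher exact tests, with the effect on an absolute scale: "The results will be presented using absolute differences and 95% confidence intervals for categorical parameters".
- Multivariable analysis of dichotomous endpoints: a "generalized linear mixed model, with logit link function, and center as random-effect".
- Effect measure from that model: "The results will be expressed with of relative risks and 95% confidence intervals".

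The following paragraph of the same section gives longitudinal data random-effects regressions with participant and session effects. The multivariable model for the primary outcome (section 3.3.1) uses session as the random effect. Centre appears as a model term only in the dichotomous model, and it is not defined.

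On where the trial is run, section 2.2.1 states "NLP and sophrology will take place within the University Hospital of Clermont-Ferrand" and section 2.2.2 states "All measures will be conducted at the CHU Clermont-Ferrand". On where participants come from, section 2.2 is broad ("We will recruit any HCW or any NHCW from a healthcare institution"), while section 2.5 sets an order: "The study will be first proposed to workers of the University Hospital of Clermont-Ferrand", and then "If there are not enough volunteers, then the study will be expanded to include all healthcare professionals".

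**The concern.** The link function and the effect measure are both fixed in the text, in adjacent sentences, and they do not agree. A relative risk comes directly from a log link, or indirectly from predicted risks. It is not the exponentiated coefficient of a logit model. An analyst who follows the article as written would print odds ratios in a column headed relative risk.

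The odds ratio always lies further from 1 than the relative risk, so the mislabelling would exaggerate the effect in either direction. The size depends on how common the endpoint is. Section 3.2.3 defines several two-level states: job strain, isostrain, an effort-reward ratio above one, and active versus inactive. Section 2.4 admits only people scoring at least 50 on the stress visual analogue scale. Some of these states may therefore be common, although the article gives no frequencies.

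A second, smaller issue is the random effect. If every participant belongs to one centre, a between-centre variance cannot be estimated and the mixed model reduces to ordinary logistic regression.

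**Working it through.** **Plan's own figure.** The article states no event rate, odds ratio or relative risk for any dichotomous endpoint, so there is no figure on this point to reproduce. The only design figure is 85 per group (section 3.1) for a standardised difference of 0.5 in heart rate variability. It reproduces by the normal approximation: 2 × (1.960 + 1.282)² / 0.5² = 84.1, rounded up to 85. It concerns a continuous endpoint and has no bearing here.

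**Step 1: what the model estimates.** With a logit link, log[p/(1−p)] = a + b·group + covariates + u(centre). Then exp(b) is the ratio of odds at fixed covariates and fixed u, which is a conditional odds ratio. The relative risk is p1/p0. The two agree only approximately, and only when the endpoint is rare.

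**Step 2: size of the gap.** Inputs: control risk p0 (assumed, 10% to 60%) and true relative risk 0.70 (assumed for illustration).

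p1 = 0.70 × p0; OR = [p1/(1−p1)] / [p0/(1−p0)]

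| p0 | p1 | Odds, intervention | Odds, control | OR | Reduction if OR is read as RR |
|---|---|---|---|---|---|
| 10% | 7% | 0.0753 | 0.1111 | 0.68 | 32% |
| 30% | 21% | 0.2658 | 0.4286 | 0.62 | 38% |
| 40% | 28% | 0.3889 | 0.6667 | 0.58 | 42% |
| 50% | 35% | 0.5385 | 1.0000 | 0.54 | 46% |
| 60% | 42% | 0.7241 | 1.5000 | 0.48 | 52% |

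The true reduction is 30% in every row. The figures are for a plain two-group comparison. An odds ratio conditional on prognostic covariates or a random effect tends to lie further from 1 still.

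In the other direction, a fitted odds ratio of 0.50 corresponds to a relative risk of 0.53 at 10% control risk, 0.59 at 30%, 0.67 at 50% and 0.71 at 60%.

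**Step 3: consistency with the absolute difference.** At p0 = 50% and p1 = 35% the absolute difference is 15 percentage points. An odds ratio of 0.538 read as a relative risk would imply 50% × (1 − 0.538) = 23 points. Two effect measures reported for the same endpoint would then disagree.

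**Step 4: the centre term.** Delivery is at one hospital (section 2.2.1), measurement is at the same hospital (section 2.2.2), and recruitment starts with its staff (section 2.5). If recruitment stops there, centre has one level and the random effect models nothing. If recruitment widens, centre could mean employing institution, but the article does not say so, and there might be only a few levels of very unequal size.

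**The case against.** The best defence is that relative risks can legitimately be obtained from a logistic model by averaging predicted risks. The article says that a separate statistical analysis plan is kept, and a conversion step is the kind of detail such a plan may hold. That stands in part: a reader might infer that odds ratios will certainly be printed as relative risks, and the text does not establish this. It shows only that link and measure are both stated and that nothing connects them.

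A reader might also infer that correlation between repeated measurements on the same person is ignored. The document does not support that. The next paragraph of section 3.3.2 gives longitudinal data participant and session random effects and is not restricted to continuous outcomes. The logit model is most naturally read as a comparison with one outcome per person.

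Nor can the centre variance be called inestimable outright. Staff of other institutions are eligible and may be recruited if volunteers are too few, so the criticism is conditional on where recruitment ends.

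Finally, the size rests on assumed risks. At 10% the gap is trivial (0.68 against 0.70). Two of the psychological scales, the anxiety and depression scale and the burn-out inventory, are described in section 3.2.3 with more than two levels and would need a cut-point before this model applied. Section 3.3 also calls most secondary analyses exploratory. All of this limits the weight of the point, but none of it reconciles the two adjacent sentences.

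**Conclusion.** The point holds in a limited form. Section 3.3.2 pairs a logit link with relative risks and names no conversion; unless an unstated step is applied, a conditional odds ratio would be reported as a relative risk. For a true relative risk of 0.70, the apparent reduction would be 32% at a control risk of 10%, 38% at 30%, 46% at 50% and 52% at 60%, against a true 30%. The control risks and the relative risk are assumptions.

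The centre random effect is undefined. It is empty if all participants come from the one hospital where the trial is delivered and measured.

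The consequence is confined to secondary, mostly exploratory endpoints. The primary endpoint is continuous, and its test, type I error and sample size are untouched. The correction is still worth making before analysis, so that the effect measure is not settled after the results are known.

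**What to change.** 1. Choose one effect measure for dichotomous endpoints and match the model to it. Either keep the logistic model and label the results as odds ratios, or report relative risks obtained by marginal standardisation from the logistic model or by modified Poisson regression with robust standard errors.
2. Drop the centre random effect. If other institutions are recruited, define centre as employing institution and enter it as a covariate.
3. State that dichotomous endpoints analysed over time use the participant and session random effects already given in the longitudinal paragraph.

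The cost is two or three sentences of analysis wording. No further participants or data are needed, and the sample size does not change.
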